Despite recurrent complaints of patients about their PM, only a few studies have focused on PM deficits in BC [2, 3, 7–10]. Paquet and colleagues used the Memory for Intention Screening Test (MIST) [11], a common PM task, composed of four EB and four TB intentions to retrieve while completing a word puzzle in the laboratory. A naturalistic task had to be carried out at home 24 h later. The authorsdid not differentiate between EB and TB intentions, but their results revealed decreased performances of patients compared to healthy women [2]. Cheng and colleagues used two laboratory tasks, assessing TB and EB intentions separately. During these tasks, participants had to tap the desk at the target time or event. Results showed a deficit in EB intention retrieval in BC patients [3, 9, 10]. Altogether, results from these studies revealed an impairment of PM in BC patients. However, none distinguished between prospective and retrospective components, which limits the understanding of the impaired processes. In addition to PM, Cheng and colleagues [4–6] assessed general cognitive functioning with Mini Mental State Examination, Verbal Fluency Test, and Digit Span test. Results revealed a significant decrease of cognitive functioning in BC patients compared with healthy women, but the authors did not correlate neuropsychological scores with PM scores. Cognitive functions known to be involved in PM functioning must be evaluated and correlated with PM scores in order to better understand the PM deficits in BC patients.

Furthermore, laboratory PM tasks lack ecological validity. Virtual reality may be suitable to assess PM because it recreates naturalistic situations of daily life while maintaining experimental rigor [6] that is difficult to uphold in naturalistic PM tasks. Other factors associated with BC (depression, stress, anxiety, and fatigue) may affect both cognition and PM [2, 12], and should therefore be taken into account to deepen knowledge about factors implicated in PM deficits in BC patients.

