## Methods

### Study objectives

The primary objective of the PROSOM-K study is to assess PM performances in BC patients, in order to determine which components (prospective or retrospective), and types of intentions (EB or TB) are the most impaired in BC patients, and specify which cognitive processes (episodic memory, working memory, or executive functions) are particularly involved in PM decline in BC patients.

The secondary objectives are to:clarify the influence of sleep disturbances in BC on PM deficits, using various sleep quality assessments (polysomnography, actigraphy and self-report questionnaires), and by comparing PM scores in two different conditions, depending on the type of delay between encoding and retrieval of intentions: day-time and night-timeassess the influence of HT on PM functioning by comparing PM scores between BC patients treated with HT and BC patients not treated with HT.

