### Statistical analysis

This study was designed to control an error risk α of 0.05 and a power of 80%. Assuming cognitive decline for 30% of BC women under HT versus 10% among healthy controls [50], the required sample size is 24 patients per group. We thus planned to enrol a total of 75 participants (25 BC patients receiving HT, 25 BC patients without indication to HT and 25 healthy women).

Descriptive statistics (relative frequency, mean value and SD) will be estimated for the socio-demographic and clinical variables from the total population included in the study. Comparison of means for sub-groups of participants will be realised by Student’s or Wilcoxon’s tests as appropriate. Comparisons of the proportions will be performed using both parametric and non-parametric tests. Link between PM and underlying cognitive functions, HT, and sleep quality, will be estimated thanks to univariate and multivariate logistic regression models, and results will be presented with odds ratios (OR) and their 95% confidence intervals (CI). All analyses will be conducted using R (version 3.4.1).

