## Discussion

Numerous BC patients survivors report memory troubles. A recurring complaint is that they forget what they are supposed to do at the right moment, referring to PM. This PM is essential for self-sufficiency and medical adherence and thus the well-being of BC patients. Few studies have been published on PM functioning in BC patients, and PM process impairment needs to be more precisely evaluated. Coupled with PM impairment, several BC patients report sleep disturbances. Few studies have used PSG to assess sleep in BC, but results have revealed a decrease of sleep quality in BC patients. Knowing the involvement of sleep in memory consolidation, these results support the necessity to investigate the link between memory impairment and sleep disturbances in BC. Furthermore, HT seems to have a negative impact on memory and sleep, but there is still a lack of research in this area.

The current study will assess PM using an innovating and ecological virtual reality based task. The different types of components and intentions will be distinguished and correlated with performances in various neuropsychological tests. These tests will assess working memory, episodic memory, and executive functions known to be involved in PM functioning. The findings are expected to improve understanding of PM impairment and underlying mechanism in BC patients. Sleep will be assessed by PSG in order to obtain additional information related to sleep architecture. Sleep architecture parameters will also be correlated to PM scores and performances at night-time and day-time sessions will be compared in order to put forward the consolidation of prospective memories during sleep. These various assessments will be performed among BC patients treated or not with HT and healthy women, so that it will be possible to bring to light the possible specific impact of either BC and/or HT on PM functioning and sleep quality.

Even though the current study aims at assessing PM using an ecological task in a virtual environment, it remains a limitation. Virtual reality may provoke uncomfortable sensations like nausea and dizziness. Session of familiarisation will allow participants to become accustomed with virtual reality. If at the end of the session 1, participants are not used to virtual reality and feel sick, the task will be stopped and they will be withdraw from the study.

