## Conclusion

The PROSOM-K trial is expected to bring multifaceted information on PM difficulties among BC patients. Indeed, the assessment of the relationship between components and intentions of PM using virtual reality, and neuropsychological tests, should lead to advanced knowledge about the PM processes impaired in BC patients. PSG data will be an opportunity to better explore the architectural sleep disturbances in BC. Thanks to the three groups of participants and the three sessions, some information should be given on the influence of sleep and HT on PM functioning. In a longer term, we expect our findings will be useful for patients and clinicians to understand and take into account their complaints, and thereby improve their take care. We also expect our results will further help to develop applications to improve their daily life and compensate for their PM impairment, as well as to improve cognitive therapy related to sleep and cognitive disorders.

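### The cognitive-process part of the primary objective is paired with a test of whether each function relates to PM at all, so a function intact in patients can be reported as involved in their PM decline

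*Protocol article*

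**What the plan says.** In the Protocol article, Study objectives, the primary objective has three parts: which PM components are most impaired, which types of intention are most impaired, and, third, to "specify which cognitive processes (episodic memory, working memory, or executive functions) are particularly involved in PM decline in BC patients".

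For the third part, Statistical analysis states: "Link between PM and underlying cognitive functions, HT, and sleep quality, will be estimated thanks to univariate and multivariate logistic regression models". Results are to be odds ratios with 95% confidence intervals. The Discussion adds that PM components and intention types will be correlated with the neuropsychological tests. No interaction, attenuation or mediation analysis is stated.

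The article also says how it will read these associations. Background holds that the functions "must be evaluated and correlated with PM scores in order to better understand the PM deficits in BC patients". The Conclusion expects that relating PM to the tests "should lead to advanced knowledge about the PM processes impaired in BC patients".

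On how the functions were chosen, the Discussion says: "These tests will assess working memory, episodic memory, and executive functions known to be involved in PM functioning".

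Statistical analysis separately plans: "Comparison of means for sub-groups of participants will be realised by Student’s or Wilcoxon’s tests as appropriate". It does not link these comparisons to the cognitive-process question.

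**The concern.** A decline in patients is a contrast with women who do not have the disease, and the matched healthy group is there to supply it. A function helps to explain that contrast if it is worse in patients and bears on PM (or if it bears on PM differently in patients). A regression or correlation of PM on the function addresses only whether it bears on PM. Its null hypothesis is that PM and the function are unrelated, and the article already regards that as false for episodic memory, working memory and executive functions.

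A significant odds ratio is therefore expected for a function that cancer has left untouched, and even if patients have no PM deficit. If that odds ratio is read as Background and the Conclusion suggest, the mechanistic conclusion of the trial would describe how PM works in general and present it as a finding about breast cancer.

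**Working it through.** The plan gives no figure for this part of the objective. Its sample-size calculation concerns proportions with cognitive decline, and this point does not depend on it. The check is how often the stated analysis flags a function that is identical in patients and controls.

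**Inputs from the article:** 50 patients (25 with and 25 without hormonal therapy), 25 healthy women, α = 0.05, impairment in 30% of hormonally treated patients and 10% of controls.

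**Assumed:** the within-group correlation r between PM and the function (0.3 to 0.6, equal in both groups), the 30% rate applied to all patients, and the cut that makes PM binary. The article gives none of these.

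**Model:** PM = r·F + √(1 − r²)·e − δ·G. F and e are standard normal, G = 1 for patients, and F has no group difference.

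- Outcome A: PM below −1.2816, the control 10th centile. For 30% of patients to fall below it, δ = 1.2816 − 0.5244 = 0.757 SD.
- Outcome B: PM split at the median, with δ = 0 or 0.6 SD.

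Share of simulated trials in which the logistic coefficient of the intact function is significant:

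| r | A, all 75 women | A, group added | A, patients only | B, all 75 (δ = 0 / 0.6) | B, patients only |
|---|---|---|---|---|---|
| 0.3 | 41% | 40% | 31% | 53% / 50% | 36% |
| 0.4 | 64% | 65% | 53% | 81% / 77% | 59–60% |
| 0.5 | 85% | 86% | 76% | 95% / 94% | 82–84% |
| 0.6 | 97% | 96% | 93% | not run | not run |

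At r = 0 the rate is about 5% in every version, so the test is valid for its own null hypothesis. Adding group as a covariate changes little. Restricting to patients lowers the rates only because n falls to 50.

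**Same function, two conditions required** (it differs between patients and controls, and it predicts the PM score given group): flagged in 4.4% to 4.6% of trials under the outcome A settings and 3.6% to 5.3% under the outcome B settings. The group comparison of the function alone is significant in 4% to 6%.

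**Power of the two-condition rule when the function really is lower in patients:**

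- 0.757 SD lower: 64% at r = 0.3, 86% at 0.5, 85% at 0.6.
- 0.8 SD lower: 86% to 90% at r = 0.4 to 0.5.
- 0.5 SD lower, by formula: the group test has non-centrality 0.5 × √(50 × 25 / 75) = 2.04, power 52%. The slope test has non-centrality r/√(1 − r²) × √75 = 2.72, 3.78 and 5.00 at r = 0.3, 0.4 and 0.5, power 77%, 96% and almost 100%. The two tests are approximately independent, so joint power is about 40%, 50% and 52%. A direct simulation gave 39%, 49% and 52%.

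**The case against.** The strongest reply is that the plan contains more than the regression. It also compares means between sub-groups, and a function intact in patients would usually show no difference there. A group difference together with an association is close to the rule recommended here. This stands in part: the ingredient is in the plan. What is absent is any statement that the two results are combined, or that the group comparison governs this conclusion.

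A second reply is that a journal article condenses the protocol, and the full document may add an interaction or mediation analysis. That is possible, and such an omission alone would not be a finding. But the article names a method for this link and states what it will be taken to show, and the two do not match.

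Third, the objective can be read as asking which functions track poor PM among patients, which a patients-only association would answer. That reading is available. The wording nevertheless refers to a decline, and the article does not say that the model is restricted to patients.

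Stronger readings are tempting but not supported:

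- A reader might set 40% to 95% against a nominal 5% and infer inflated type I error. In these simulations PM and the function are truly related, so the rates are power.
- A reader might infer that the trial will name causes. The objective speaks only of involvement, and no rule turns a significant odds ratio into a claim about the deficit.
- A reader might take this to undermine the whole primary objective. It concerns one of three parts.

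**Conclusion.** The concern holds in this limited form. The stated analysis for one part of the primary objective cannot distinguish a function that contributes to the patients' PM decline from one that PM uses in all women. A function intact in patients can, and quite likely will, be reported as involved in the decline.

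For such a function, the association in all 75 women is significant in roughly 40% to 95% of trials at r = 0.3 to 0.5: 41% to 85% with 30%/10% impairment and 50% to 95% with a median split. Requiring a group difference as well brings this to about 4% to 5%. The size rests on the assumed r, on equal slopes in patients and controls, and on the assumed cut of PM. The mismatch between question and test rests on the text alone. It should be corrected because it changes what the trial can conclude about mechanism.

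**What to change.** State that a cognitive process will be reported as involved in the PM decline only if (a) its score differs between BC patients and healthy women and (b) it predicts the PM score in a model that includes group. Name the score that represents each domain (episodic memory, working memory, executive functions) in advance.

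As a supportive estimate, fit a linear model of the PM score on group, then on group plus the domain score. Report the change in the patient-control PM difference with a bootstrap 95% confidence interval, described as non-causal. Label plain regressions and correlations as functions related to PM. The minimum alternative is to reword this part of the objective as associational.

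The change costs analysis wording only: Table 3 marks only FACT-G and FACIT-F as patient-only, so the cognitive scores are planned in all groups. Fewer processes will be declared, and power is about 40% to 50% if the function is 0.5 SD lower in patients. The rule can miss a process whose slope, rather than level, differs in patients. The estimate remains observational: the groups are not randomised, and Table 1 requires a MoCA score of at least 26 of healthy women but not of patients, so part of a group difference may reflect selection.

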### Outcome measures

#### PM task

During the learning of each of the 9 intentions (3 per type of intention, i.e. 3 linked EB, 3 no-linked EB, and 3 TB), a score [0–1] will be attributed per intention for the first cued recall (see Table 2). We will also evaluate the number of repetitions needed to correctly recall all intentions. The maximum total PM encoding score of each session will be 9 points, corresponding to the sum of the points attributed for each intention (1point * 9 intentions).

During the retrieval of the 9 intentions, a score [0–6] will be attributed for each intention corresponding to the points allocated for the prospective component [0–2], the retrospective component [0–2], and the associative component (i.e., the simultaneous retrieval of prospective and retrospective components) [0–2] (see Table 2). The maximum total PM retrieval score of each session will be 54 points, corresponding to the sum of the maximal scores attributed for each intention (6 points * 9 intentions).

**Table 2 Tab2:** Scoring of each intention of the PM task

LEARNING SCORE [range]			
1 point	Intention is correctly recalled during the immediate cued recall [0–1]		
RETRIEVAL SCORES [range]			
	Prospective [0–2]	Retrospective [0–2]	Associative [0–2]
2 points	Action realised at the first passage in front of the cue or at the right time	Retrospective component is complete	Prospective and retrospective components are recalled together
1 point	Action realised at the second passage or at +/− 1 min	Retrospective component is incomplete (one element is incorrect or forgotten)	–
0.5 point	Action is realised at a subsequent passage or at +/− 2 min	–	–
0 point	Action is not realised	Retrospective component is not retrieved	Prospective and retrospective components are not recalled together

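### Prospective memory is scored 0–54, but its only adjusted analysis is logistic regression with odds ratios, and the article defines no binary outcome per participant

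*Protocol article*

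**What the plan says.** The PM task part of Outcome measures gives each of nine intentions 0–6 retrieval points, made up of 0–2 each for a prospective, a retrospective and an associative component. It adds that "The maximum total PM retrieval score of each session will be 54 points". In Table 2 the prospective component has four levels and the retrospective component three. The associative component (0 or 2) and the learning score (0 or 1) have two levels per intention.

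The Statistical analysis section names the model for "Link between PM and underlying cognitive functions, HT, and sleep quality": these "will be estimated thanks to univariate and multivariate logistic regression models, and results will be presented with odds ratios (OR"), with 95% confidence intervals. The same section plans Student or Wilcoxon tests for sub-group means. The Discussion says that PM components and intention types will be correlated with neuropsychological performance, and that "Sleep architecture parameters will also be correlated to PM scores".

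The only binary quantity with a stated rate is in the sample-size sentence: "Assuming cognitive decline for 30% of BC women under HT versus 10% among healthy controls". It is not tied to the PM task.

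**The concern.** Ordinary logistic regression needs a two-valued outcome. The outcome section gives a graded total and graded sub-scores, and nothing in the article turns them into a yes/no result for each woman. The model family and effect measure are stated, so this is a choice the article makes and not a detail left to a fuller document.

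The choice bears on real objectives. Part of the primary objective is to find which of episodic memory, working memory and executive functions is involved in PM decline, and the secondary objectives concern sleep and HT. The logistic model is the only regression, and the only adjusted analysis, named for them. With 75 women, cutting a score in two discards information and leaves few events for a multivariable model. The odds ratios would also depend on where the cut is placed.

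**Working it through.** **Plan's own figures.** The article gives none for the regression: no cut-off, event count or number of predictors. The nearest is the sample-size statement, "the required sample size is 24 patients per group". A two-sided comparison of 30% with 10% at 5% and 80% power does not reproduce it: [1.960·√(2·0.2·0.8) + 0.842·√(0.3·0.7 + 0.1·0.9)]² / 0.2² = 61.6, so 62 per group. That is a separate matter, and nothing below depends on it.

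**Inputs from the article.** Enrolment of "25 BC patients receiving HT, 25 BC patients without indication to HT and 25 healthy women" (75 in all); rates of 30% with HT and 10% in healthy women.

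**Assumptions.** (a) The cognitive-decline rates are applied to a PM cut. (b) The rate in patients without HT, which is not given, lies between 10% and 30%. (c) The model has five slopes: three cognitive processes, HT and one sleep variable. (d) The score is roughly normal.

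**Step 1, events.** In all 75 women: 25·0.30 + 25·0.10 + 25·(0.10 to 0.30) = 12.5 to 17.5, a prevalence of 16.7% to 23.3%. In the 50 patients: 25·0.30 + 25·(0.10 to 0.30) = 10 to 15. A median split of 75 puts 37 in the smaller class.

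**Step 2, events per slope.**

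| Case | 5 slopes | 6 slopes |
|---|---|---|
| 75 women, 12.5–17.5 events | 2.5–3.5 | 2.1–2.9 |
| 50 patients, 10–15 events | 2.0–3.0 | 1.7–2.5 |
| 75 women, median split, 37 | 7.4 | 6.2 |

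**Step 3, information kept.** For a normal score cut at prevalence p, the fraction kept is φ(z_p)² / [p(1−p)].

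| p | Kept | Lost | 75 women are worth |
|---|---|---|---|
| 16.7% | 0.450 | 55% | 33.7 |
| 20% | 0.490 | 51% | 36.7 |
| 23.3% | 0.524 | 48% | 39.3 |
| 50% | 0.637 | 36% | 47.7 |

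**Step 4, simulation check.** 1,000 runs with n = 75, a normal score, six independent continuous covariates and a true correlation of 0.33 for one of them, tested at 5%. Power was 79–81% with linear regression. With logistic regression it was 46% at 16.7% prevalence, 45% at 20%, 52% at 23.3% and 61% at a median split. The Monte Carlo standard error is at most √(0.25/1000) = 1.6 points. The result agrees with Step 3. Failed or extreme fits were rare, at no more than 1 in 1,000.

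**Step 5, modelling the score.** With six slopes there are 75/6 = 12.5 women per slope, and nothing is lost to a cut.

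**The case against.** The strongest reply has four parts.

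- **PM is also analysed as a score.** A reader might infer that every PM analysis is dichotomised. The documents do not support that: tests of means and correlations are planned and can stand beside a logistic model. This stands, and limits the point to the regression and adjusted results. It also rules out charging the group comparison with a loss of power, because the plan tests sub-group means directly.
- **Logistic need not mean a cut total.** An ordinal logistic model gives odds ratios without a cut, and the two-level associative and learning items could be modelled per intention. Under either reading, Steps 1 to 3 do not apply. This stands as a possibility, but the article states neither. Item-level models would also cover only part of the graded retrieval score.
- **The figures are scenarios.** A reader might take a loss of about half the information and 2–3 events per parameter as facts of the plan. They are not: the rates concern cognitive decline, the rate without HT and the slope count are assumed, and a median split is milder. This stands in full. Yet the median split still loses 36%, so no single cut of a normal score removes the problem.
- **An article condenses.** A cut-off may exist in the full protocol or analysis plan. Its absence here is therefore not the finding. The finding is the stated model, which would still discard information if a cut were documented.

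A reader might also infer that the models would break down through separation. The simulation gives no support for that with continuous covariates.

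**Conclusion.** The concern holds in limited form, as something that should be fixed. The article commits its only adjusted PM analysis to a model that does not match the 0–54 score it defines, while its other PM analyses use the score.

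If PM is dichotomised, the loss of information runs from 36% at a median split to 48–55% at 17–23% prevalence. With five slopes, events per slope run from about 7 down to 2.5–3.5 in all women, or 2–3 among patients only. At these counts adjusted odds ratios would be imprecise and prone to small-sample bias, which was not quantified here. The size depends on the four assumptions above. The mismatch between model and outcome depends on none of them, unless an ordinal or item-level model was meant and not stated.

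**What to change.** In the Statistical analysis section, replace the logistic models by linear regression on the PM retrieval score and its sub-scores. Report slopes and adjusted mean differences with 95% confidence intervals. Name an ordinal, rank-based or bootstrap alternative in case scores pile up at the ceiling. If an ordinal logistic model was intended, saying so would also settle the point.

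State a short predictor set in advance, sized to 75 women. One example is group (two terms), one score for each of the three cognitive domains and one sleep variable: 2 + 3 + 1 = 6 slopes. Limit polysomnography predictors to the night-time session score, since it is recorded only for that session. Align the paragraph with the score-based correlations in the Discussion.

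The cost is a change of wording, with no new data, visits or participants. The downside is that results appear in score points and not as odds ratios.
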